## Abstract

**Background:**

Hypoxemia is a major complication in obese patients undergoing gastrointestinal endoscopy under intravenous anesthesia or sedation due to altered airway anatomy. We design this randomized controlled trial (RCT) to compare efficacy and safety of the Wei nasal jet tube (WNJT) and nasal prongs for supplement oxygen during gastroscopy with intravenous propofol anesthesia in obese patients.

**Methods:**

The study will be a single-center, prospective RCT. A total of 308 obese patients will be recruited and randomly assigned to receive either the WNJT (group A) or nasal prongs (group B). During gastroscopy with intravenous propofol anesthesia, 5 L/min of oxygen will be delivered through the jet port of the WNJT in the group A and via the nasal prongs in the group B. The primary outcome is the incidence of hypoxemia and severe hypoxemia. The secondary outcomes are adverse events during the gastroscopy, postoperative complications, and satisfaction of the anesthetist, physician, and patient.

**Discussion:**

This RCT aims to clarify whether the WNJT can result in reduced incidences of hypoxemia and complications and provide improved satisfaction to the anesthetist, physician, and patient. Thus, it can be determined if the WNJT is a useful tool for supplement oxygen in obese patients undergoing gastroscopy with intravenous propofol anesthesia. The results will provide the evidence for anesthesiologists to make a decision regarding the choice of supplementary oxygen methods in this condition.

**Trial registration:**

Chinese Clinical Trial, ChiCTR-IOR-17013089. Registered on 23 October 2017.

**Electronic supplementary material:**

The online version of this article (10.1186/s13063-018-2994-8) contains supplementary material, which is available to authorized users.

## Background

Gastroscopy is an important and commonly used upper gastrointestinal examination. It enables physicians to visualize a variety of upper gastrointestinal lesions and is the standard tool for the diagnosis and treatment of many gastrointestinal diseases [1, 2]. However, patients are often reluctant to undergo routine gastroscopy due to its uncomfortable experience and adverse outcomes such as nausea, vomiting, anxiety, throat bleeding, etc [3]. Thus, intravenous sedation or anesthesia with short-acting intravenous anesthetics such as propofol has been recommended in the international guidelines for gastrointestinal endoscopy [4–6].

The use of intravenous sedation or anesthesia can improve patients’ comfort during gastrointestinal endoscopy, but hypoxemia is common during endoscopy with intravenous sedation or anesthesia due to respiratory depression, airway obstruction, and hemodynamic instability [7]. In particular, hypoxemia is more common in obese patients because of altered airway anatomy, such as short neck, limited neck extension, and fat deposition in the pharyngeal wall [7, 8]. As hypoxemia significantly contributes to cardiopulmonary complications, morbidity, and mortality during gastrointestinal endoscopy with intravenous sedation or anesthesia [9, 10], prevention of hypoxemia is a key step to a safe procedure. Furthermore, the international guidelines for gastrointestinal endoscopy recommend that the supplemental oxygen reduces the incidence of hypoxemia during gastrointestinal endoscopy with intravenous sedation or anesthesia [4–6].

A regular nasal cannula oxygen supply helps to reduce the incidence of hypoxemia during gastrointestinal endoscopy with intravenous sedation or anesthesia, but is inadequate for patients with increased risk factors for hypoxemia [8, 11]. Mask ventilation is difficult or even impossible during upper gastrointestinal endoscopy due to the endoscope in the mouth. Furthermore, during gastrointestinal endoscopy with intravenous sedation or anesthesia, upper airway obstruction due to soft-tissue collapse or tongue falling is a major concern [12], particularly for obese patients [7, 8]. For this reason, the placement of a nasopharyngeal airway may be a good solution as it can be conveniently inserted and ensures an open airway [13]. A prospective randomized study by Xiao et al. [14] evaluated the efficacy and safety of the nasopharyngeal airway relative to the nasal cannula in obese patients undergoing gastroscopy with intravenous anesthesia and showed that the amount of reduction in pulse oxygen saturation (SpO_2_) from baseline during gastroscopy was significantly less in the nasopharyngeal airway group (6.03%) than in the nasal oxygen tube group (10.46%).

The Wei nasal jet tube (WNJT; Well Lead Medical Co. Ltd., Guangzhou, China; Fig. 1) is a new special nasopharyngeal airway. Compared with the convenient nasopharyngeal airway, the WNJT can be connected to an anesthesia machine directly and pure oxygen can be delivered through its jet port. Furthermore, the WNJT has a small channel built inside the tube wall for monitoring the end-tidal partial concentration of carbon dioxide (P_ET_CO_2_), which can be used as a sign to identify the existence of a smooth flow in the airway and the occurrence of respiratory depression during gastroscopy with intravenous anesthesia or sedation [15, 16]. Currently, there are two types of commercial WNJTs available for adult patients, with the inner diameters of 5.0 mm and 7.0 mm, the outer diameters of 7.3 mm and 10.0 mm, and the lengths of 145 mm and 155 mm.

**Fig. 1 Fig1:**
[figure not shown]
Wei nasal jet tube

In the available literature, one multicenter, randomized controlled trial (RCT) has assessed the influences of supplement oxygen with the WNJT on respiration and ventilation during upper gastrointestinal endoscopy with propofol sedation in patients with a normal body mass index. This study shows that supplement oxygen with the WNJT compared with nasal cannula oxygen can significantly decrease the use of jaw-thrust maneuver but does not affect the incidences of total adverse events, subclinical respiratory depression, hypoxia, severe hypoxia, and mask ventilation [15]. Furthermore, it has been shown that the supraglottic jet ventilation by the WNJT during upper gastrointestinal endoscopy for patients who are sedated with propofol reduces the incidence of hypoxia in normal patients [15] and a morbidly obese patient [17]. However, there has been no study having determined the influences of supplement oxygen with the WNJT on respiration and ventilation during upper gastrointestinal endoscopy with propofol sedation or anesthesia in obese patients. In addition, placement of the WNJT is an invasive procedure and may result in a potential risk of nasal injury and bleeding [14]. Considering that there are limited data on the use of the WNJT during upper gastrointestinal endoscopy with intravenous sedation or anesthesia in obese patients and no study has assessed whether the WNJT performs better than the convenient nasal prongs for supplement oxygen in this condition, this RCT is designed to compare the efficacy and safety of the WNJT versus nasal prongs for supplementary oxygen during gastroscopy with intravenous propofol anesthesia in obese patients.

## Methods/design

The flow chart of this study is shown in the Fig. 2.The SPIRIT Checklist and Figure are presented as Additional file 1 and Fig. 3, respectively.

**Fig. 2 Fig2:**
[figure not shown]
*Flow chart* of present study

**Fig. 3 Fig3:**
[figure not shown]
The SPIRIT figure

### Trial design

This study is a single-blinded, prospective RCT. The protocol has been approved by the Ethics Committee of Beijing Friendship Hospital, Capital Medical University, Beijing, China (Ethics Committee number: 2017-P2–009-02) and is registered with Chinese Clinical Trial Registry (http://www.chictr.org.cn/; registration no. ChiCTR-IOR-17013089). The patients will be recruited from the Gastroenterology Clinic of Beijing Friendship Hospital. All patients who participate in the study must provide their written informed consent.

### Setting

The Gastroenteroscopy Center of Beijing Friendship Hospital, Capital Medical University, Beijing, China.

### Participants

The inclusion criteria are male or female patients aged 18–65 years, with the American Society of Anesthesiologists (ASA) physical status classifications I–II and BMI ≥ 30 kg/m^2^. Exclusion criteria are: coagulopathy or nose bleeding; severe cardiac, pulmonary, hepatic, or renal diseases; infection of the mouth, nose, or throat; allergy to propofol, eggs, soybean, or albumin, and others.

### Randomization and blinding

According to a random number table generated by a computer, patients are randomly assigned to receive either the WNJT (group A) or the nasal prongs (group B). An online random list generation will be utilized to perform blocked randomization in a 1:1 ratio. Outcome assessment and statistical analysis will be performed by independent researchers who are from the Clinical Research Institute of Beijing Friendship Hospital and are blind to the group assignment.

### Interventions

All patients are fasted for 8 h before the gastroscopy. After patients enter into the examination room, a topical anesthesia of oral cavity and pharynx is performed by gargling 2% lidocaine gel (10 g:0.2 g; Jumcan Pharmaceutical Group, China); two sprays of ephedrine to the nasal mucosa of each nostril are applied in all patients as to our practice. Heart rate (HR), blood pressure (BP), and SpO_2_ are continuously monitored. After establishing an intravenous access, patient is placed at the lateral position as is the routine practice of our hospital for gastrointestinal endoscopy. Preoxygenation is then performed until an end-tidal oxygen concentration of 88–90% is reached. To facilitate preoxygenation, the patient is intermittently asked to take eight deep breaths in 60 s with 100% oxygen [18]. The end-tidal concentrations of oxygen and carbon dioxide during preoxygenation are continuously monitored by a gas analyzer of anesthesia machine.

After adequate preoxygenation, anesthesia is induced with intravenous injection of propofol 2 mg/kg (10 mg/1 mL; Diprivan, Astrazeneca, UK). The depth of anesthesia is assessed by an anesthesiologist blinded to the group assignment. During the gastroscopy, 20–30 mg of propofol are supplemented as necessary to maintain an Observer’s Assessment of Alertness/Sedation score of 2 or 3 [19]. For patients receiving the WNJT, an appropriate size (ID 5.0 or 7.0 mm) device is selected by examining the outer diameter of the device and the patient’s nostrils. The device that is large enough but can be easily inserted through the nostril is selected. The WNJT is lubricated with 2% lidocaine gel (Jumcan Pharmaceutical Group, China) before insertion. The distance between the tip of the nose and earlobe on one side is measured using the scale on the exterior wall of the WNJT. After adequate anesthesia is achieved, the WNJT is inserted to the measured depth in the group A and the nasal prongs are placed in the group B. The position of the WNJT is re-examined by gastroscopy and adjusted for appropriate if necessary. The ideal position is designed as the distal tip of the WNJT is within 1 cm of the epiglottis tip. If insertion of WNJT is difficult via the selected nasal passage, the other side can be tried. If it is still unsuccessful after three attempts, insertion of the WNJT is regarded as a failure. During the gastroscopy, 5 L/min of oxygen is delivered directly through the jet port of the WNJT without using a jet ventilator in the group A and via the nasal prongs in the group B, respectively. Both the WNJT and nasal prongs are removed before the patients recover consciousness. Consequently, the patients are also blinded to the grouping assignment.

Throughout the gastroscopy, if hypoxemia (SpO_2_ < 90%) occurs, the taken measures include [4–6]: (1) audio or painful stimulation; (2) no additional drugs; (3) increasing the volume of oxygen from 5 to 8 L/min; (4) airway opening with the jaw-thrust maneuver; (5) removing the gastroscope tube and performing facemask ventilation; and (6) tracheal intubation for mechanical ventilation if necessary.

During the study, if nasal bleeding occurs in the group A, compression hemostasis is first performed; if it does not work, other medical or surgical measures should be considered.

### Data collection

#### Patients’ information

Demographic data of patients—including age, gender, body mass index, history of hypertension, diabetes, and coronary artery disease—are collected from the medical records. Airway conditions, ASA physical status classifications, BP, HR, and SpO_2_ before anesthesia are assessed and recorded by a research assistant.

#### Data about the procedure

The BP, HR, and SpO_2_ during the endoscopy are recorded every 2 min. Total propofol dose, recovery time, hypoxemia, severe hypoxemia, times required for use of assistant airway maneuvers (jaw-thrust, mask ventilation, and tracheal intubation), adverse events during the endoscopy procedure (body movement, vomiting, regurgitation and aspiration, bronchospasm, cough, bradycardia, tachycardia, hypertension, hypotension), nasal bleeding, and recovery delay are also recorded.

In this study, hypoxemia is defined as SpO_2_ of 75–89% for < 60 s, and severe hypoxemia is defined as SpO_2_ < 75% at any time or SpO_2_ of < 90% for > 60 s [20, 21]. Hypotension is defined as a decrease in mean arterial pressure (MAP) > 20% or non-invasive blood pressure of not more than 90/60 mmHg; hypertension is defined as an increase in MAP > 20% or non-invasive blood pressure of at least 140/90 mmHg; bradycardia is diagnosed if HR is < 50 beats/min; tachycardia is diagnosed when HR stays above 100 beats/min. If necessary, ephedrine or phenylephrine, urapidil, atropine, and esmolol were intravenously injected to treat hypotension, hypotension, bradycardia and tachycardia, respectively [21–23].

Nasal bleeding is assessed using a subjective scale: 0, no bleeding; 1, minimal bleeding not requiring suctioning; 2, moderate requiring suctioning but not hampering visualization, and 3, severe requiring suctioning and hampering visualization [24].

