### Study outcomes

#### Primary outcome

The primary outcome is the incidence of hypoxemia and severe hypoxemia [20].

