### Sample size estimation and statistical analysis

The sample size is calculated with the Pass software (version 11.0, NCSS, LLC, Kaysville, UT, USA). The two independent proportions procedure is used. With an α = 0.05 and a power of 80%, we estimated that 140 patients per group would be required for our study. If the dropout rate is set at about 10%, a total of 308 patients (154 in each group) would be required. The incidence of hypoxemia during gastroscopy in obese patients with intravenous propofol anesthesia has been reported to be 22% [20]. Thus, a proportion of 22% of the patients in the group B is expected to develop hypoxemia. P1 and P2 are calculated from the assumption that the WNJT would achieve a reduction from 22% to 11% for the incidence of hypoxemia.

Statistical analysis of data will be performed using the SPSS (Version 23.0, SPSS Inc., Chicago, IL, USA) by a blinded statistician. Continuous variables will be presented as mean ± standard deviation (normally distributed data) or medians and ranges (non-normally distributed data). Numerical data will be compared using a Student’s t-test (normally distributed data) or Mann–Whitney rank sum test (non-normally distributed data). Qualitative data will be expressed as n (%) and compared using a Chi-squared test. A *P* value < 0.05 is considered statistically significant.

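### Hypoxemia is defined so as to exclude the worse desaturations, the trial is sized on that word alone, and the protocol does not say whether the primary outcome is one combined event or two

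*Protocol article*

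**What the plan says.** Four places in the protocol article bear on this.

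- **Data about the procedure** sets the trial's own definitions: "hypoxemia is defined as SpO_2_ of 75–89% for < 60 s, and severe hypoxemia is defined as SpO_2_ < 75% at any time". The severe class also takes in any SpO2 below 90% that lasts more than 60 s. The two classes are listed as separate recorded items. No rule is given for a patient who has both kinds of episode.
- **Primary outcome**: "The primary outcome is the incidence of hypoxemia and severe hypoxemia". It does not say whether this is one combined event or two outcomes.
- **Sample size estimation and statistical analysis**: "a proportion of 22% of the patients in the group B is expected to develop hypoxemia", and it is assumed that "the WNJT would achieve a reduction from 22% to 11% for the incidence of hypoxemia". No rate or power is given for severe hypoxemia or for a combined event.
- **Interventions** uses hypoxemia, in the rescue instructions, for any SpO2 below 90%, with no lower limit and no duration.

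**The concern.** Under the study's own definition, hypoxemia is a middle class: worse than no desaturation, better than severe. The incidence of a middle class does not have to fall when patients do better. A device that makes desaturations shallower or shorter moves patients out of the severe class and into this one. A patient whose only episode is deep or prolonged is not a hypoxemia case at all.

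Such a shift is plausible here. The Background cites a smaller drop in SpO2 from baseline with a nasopharyngeal airway than with a nasal oxygen tube (6.03% against 10.46%), which is an effect on depth.

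If the comparison the trial was sized for is made on this class, it could be null or point the wrong way while patients benefit. The benefit would then appear only in severe hypoxemia, for which nothing was planned numerically.

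**Working it through.** **Step 1: the plan's own figure.** Inputs from the sample size section are p_B = 0.22, p_A = 0.11, α = 0.05 and power 80%. Allocation is 1:1 (Randomization and blinding). The section says "With an α = 0.05 and a power of 80%, we estimated that 140 patients per group would be required" and does not give the sidedness. With the pooled formula and mean rate p̄ = 0.165:

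n = [z_α √(2p̄(1−p̄)) + z_β √(p_B(1−p_B) + p_A(1−p_A))]² / (p_B − p_A)²

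- One-sided: [1.645 × 0.5249 + 0.842 × 0.5191]² / 0.0121 = 1.691 / 0.0121 = 139.7, so 140. This matches.
- Two-sided: [1.960 × 0.5249 + 0.842 × 0.5191]² / 0.0121 = 2.148 / 0.0121 = 177.6, so 178.

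The stated 140 is therefore reproduced one-sided. I show both versions below and use 140 per group, the number required before the dropout allowance (140 × 1.1 = 154).

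**Step 2: direction.** Let m be the percentage points of mild events that the WNJT prevents, and c the points of severe events that it turns into mild ones. The mild-class rate on the WNJT equals the rate on prongs − m + c. It is flat when c = m and rises when c > m. Example with assumed figures: group B has 22% mild plus 10% severe, and the WNJT prevents nothing but converts 80% of severe cases. The mild class becomes 22 + 8 = 30% against 22%, while severe falls from 10% to 2%.

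**Step 3: power, as an illustration.** Assumptions, none of them in the documents:

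- 22% is the group B rate of any SpO2 below 90%.
- A share s of those patients is severe.
- Every severe patient is left out of the mild class.

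Power is exact for the chi-squared comparison (one-sided: the corresponding z test). On any SpO2 below 90%, 22% against 11%, it is 0.709 two-sided and 0.805 one-sided.

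*Both classes halve:* mild class 0.22(1−s) against 0.11(1−s).

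| s | Rates | Two-sided | One-sided |
|---|---|---|---|
| 10% | 19.8% v 9.9% | 0.654 | 0.760 |
| 20% | 17.6% v 8.8% | 0.593 | 0.711 |
| 30% | 15.4% v 7.7% | 0.527 | 0.657 |
| 40% | 13.2% v 6.6% | 0.455 | 0.596 |
| 50% | 11.0% v 5.5% | 0.379 | 0.528 |

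*Extreme case:* any SpO2 below 90% halves and no severe event is left on the WNJT, so the mild class is 0.22(1−s) against 0.11. Two-sided power is 0.538, 0.353, 0.192, 0.086 and 0.049 for s = 10% to 50%. At s = 50% the class reads 11% against 11% although desaturations have truly halved.

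**Step 4: the other reading of the 22%.** If 22% is already the mild-class rate, the rate and the analysed class match. A halving to 11% then keeps the planned power, and no power is lost unless patients shift between classes.

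**The case against.** The strongest reply is that the primary outcome names both classes. Read as one combined event, it is any SpO2 below 90% (apart from an episode of 75–89% lasting exactly 60 s, which neither class covers), and the rescue instructions use the word in that sense. On that reading the problem disappears. Read as two outcomes, severe hypoxemia is itself primary, so a shift from severe to mild would show there. This stands, and it limits the point. But the protocol fixes neither reading, its explicit definition is the exclusive one, and the sample size gives a rate for hypoxemia only.

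Three further limits also stand. The definition works per episode, and with no patient-level rule a patient with both a brief mild and a severe episode could count in both classes, which softens the loss. The severe share and the event behind the cited 22% cannot be seen in the document. The extreme case needs every severe event on the WNJT to vanish, which nothing in the protocol supports.

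A reader might infer that the definition is shown to make the primary comparison fail or point the wrong way. The document does not support that: it shows a comparison that could behave so under one of the open readings. Nor is the gap between 80% and 71% on the any-event outcome due to this definition; it comes from one-sided against two-sided testing.

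**Conclusion.** The point holds as an unresolved inconsistency with a real statistical consequence: four sections use one word in ways that lead to different primary events, and on the exclusive definition the powered count leaves out the worst patients and need not fall with benefit. Its size cannot be fixed from the protocol. Under the stated assumptions, excluding severe patients takes two-sided power at 140 per group from 71% to between 65% and 38% if both classes halve (one-sided, from 80% to between 76% and 53%). In the extreme case two-sided power is 54% to 5%. If the 22% is a mild-class rate, the risk is confined to a shift between classes. This should be fixed, with medium confidence; the document does not show that the trial is invalid as planned.

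**What to change.** Reconcile the definitions, the primary outcome and the sample size section. Define the primary event as at least one SpO2 below 90% of any depth or duration during the procedure, scored once per patient as yes or no. Report the worst class per patient as a breakdown, with severe hypoxemia as the key secondary outcome. The wording of the rescue instructions must be reconciled with the outcome terms as well; this is a matter of terminology and implies no change to the rescue rule.

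State which event the 22% describes. If it is any SpO2 below 90%, the required number does not change on this account. If it is the mild class only, restate the power for the combined event. For assumed group B rates of 25%, 27% or 32%, halved on the WNJT, the required number per group is 120, 109 or 88 one-sided and 152, 138 or 111 two-sided.

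The cost is an amendment to the registered primary outcome during recruitment, and a headline rate that mixes brief and severe episodes, which the breakdown makes visible. No new data are needed, because both classes are already recorded. The article reports 20 participants recruited by 10 May 2018. The change should be made before the interim analysis at half enrolment.

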#### Data after the procedure

Satisfaction of the anesthetist, physician, and patient is assessed using a 10-point visual analog scale at the time of patient’s consciousness recovery and 30 min after consciousness recovery, respectively, and classed as follows: poor, 1–4; fair, 5–7; and good, 8–10 [25]. Adverse events such as sore throat, nasal bleeding, nausea, and vomiting are also collected at the time when the patient recovers consciousness and 30 min after the recovery of consciousness.

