#### Secondary outcomes

The secondary outcomes are the adverse events during the gastroscopy, nasal bleeding or injury, complications, and satisfaction of the anesthetist, physician, and patient.

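### The stated rules lead to an unordered Chi-squared comparison of three satisfaction classes, although a 10-point score is collected and a rank test is already listed

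*Protocol article*

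**What the plan says.** Under Data after the procedure: "Satisfaction of the anesthetist, physician, and patient is assessed using a 10-point visual analog scale". The same sentence then has the result "classed as follows: poor, 1–4; fair, 5–7; and good, 8–10". The article describes no other handling of the score.

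Secondary outcomes closes its list with "complications, and satisfaction of the anesthetist, physician, and patient".

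Sample size estimation and statistical analysis assigns tests by type of data only. For categories: "Qualitative data will be expressed as n (%) and compared using a Chi-squared test". For measurements: "Numerical data will be compared using a Student’s t-test (normally distributed data) or Mann–Whitney rank sum test (non-normally distributed data"). No ordinal or trend test for categories is named.

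The article has a second ordered scale, under Data about the procedure: "Nasal bleeding is assessed using a subjective scale: 0, no bleeding", rising to 3 for severe bleeding. Nasal bleeding or injury is also a secondary outcome, but the article does not say whether its grade or its incidence is compared.

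**The concern.** Once a 1–10 score has been cut into poor, fair and good, it is qualitative data under the article's own scheme, and the one test given for such data treats the classes as unordered. Information is lost twice. The cut discards differences within a class: a 5 and a 7 become equal, as do an 8 and a 10. The test then discards the fact that fair lies between poor and good.

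At stake is the ability to see a modest, consistent difference in satisfaction. The abstract gives improved satisfaction as one of the things the trial should clarify, and the data to detect it will have been collected.

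**Working it through.** **The plan's own figure.** The article gives no power or sample size for satisfaction. Its only figure is for hypoxemia: "With an α = 0.05 and a power of 80%, we estimated that 140 patients per group would be required for our study", on the assumption that "the WNJT would achieve a reduction from 22% to 11% for the incidence of hypoxemia". With pooled p = 0.165:

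n = [z(1−α)·√(2 × 0.165 × 0.835) + z(0.80)·√(0.22 × 0.78 + 0.11 × 0.89)]² / 0.11²

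- One-sided α = 0.05: (1.645 × 0.5249 + 0.8416 × 0.5191)² / 0.0121 = 139.8, so 140, as stated.
- Two-sided: (1.960 × 0.5249 + 0.8416 × 0.5191)² / 0.0121 = 177.6, so 178.

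Sidedness is a separate matter. Here 140 serves only as the number analysed per group.

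**Inputs for satisfaction.**
- From the article: scale 1–10; classes 1–4, 5–7, 8–10; 1:1 allocation; significance at P < 0.05; 140 per group.
- Assumed, because the article gives none: mean, SD and shift. Scores are drawn as normal, rounded, and limited to 1–10. Tests are two-sided.

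**Check 1: shift of 0.5 points, SD 1.5–2.0.** The standardised shift runs from 0.5/2.0 = 0.25 to 0.5/1.5 = 0.33. Simulated power is about 33–46% for Chi-squared on the three classes and 50–76% for Mann–Whitney on the raw score. The Chi-squared range depends on the assumed means; another set of means gave up to 53%, with 50–75% for raw ranks. In one worked case (means 8.0 and 7.5, SD 1.7) the results are about 42% for Chi-squared, 52% for ranks on the classes and 65% for ranks on the raw score. A rough check of the last figure: (0.5/1.7) × √(140/2) − 1.96 = 0.50, which is 69% power for unrounded normal data.

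**Check 2: shift of 0.337 SD.** This is the shift that gives a t-test about 80% power with unrounded data: 0.337 × √70 − 1.96 = 0.86. Power in %, 3,000 runs per row:

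| Mean, SD | Chi-squared, 3 classes | Mann–Whitney, 3 classes | Mann–Whitney, raw score |
|---|---|---|---|
| 5.5, 1.5 | 58.1 | 68.7 | 78.2 |
| 5.5, 2.0 | 60.2 | 71.1 | 77.7 |
| 6.5, 1.5 | 55.1 | 65.5 | 76.5 |
| 6.5, 2.0 | 58.4 | 69.1 | 77.3 |
| 7.5, 1.5 | 52.3 | 63.1 | 77.3 |
| 7.5, 2.0 | 52.9 | 64.3 | 77.3 |
| 8.5, 1.5 | 43.5 | 50.1 | 73.5 |
| 8.5, 2.0 | 44.7 | 55.3 | 74.3 |

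Ignoring order costs about 7–11 points (for example 50.1 − 43.5 = 6.6; 64.3 − 52.9 = 11.4). Cutting into classes costs a further 7–23 (77.7 − 71.1 = 6.6; 73.5 − 50.1 = 23.4). The total is about 18–30. The loss is greatest when most scores are high and fall in the good class. With no true difference, the Chi-squared test rejected in 3.7–5.6% of runs, so validity is not in question.

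**Check 3: other kinds of difference.**
- With a shift of 1.0 point the gap nearly closes: about 95% for Chi-squared, 97% for ranks on classes and 99.8% for raw ranks.
- Suppose both groups score about 8.5 (SD 1.2), but a minority of one group scores 2–4. Chi-squared then has 76% power against 11–13% for raw ranks when the minority is 5%, 93% against 19% at 7%, and nearly 100% against 31% at 10%.
- The reason shows in the counts. A 5% minority is 7 of 140 against practically none. For 7 against 0 in the poor class alone, Pearson's statistic is 280 × (7 × 140)² / (140 × 140 × 7 × 273) = 7.2, above the 5.99 needed on 2 degrees of freedom. The mean moves by only about 0.05 × (8.5 − 3) = 0.28 points.

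**Bleeding grade, if it is compared.** Assume bleeding in 10% of group A and 1% of group B. That is 14 + 1.4 = 15.4 patients, or an expected 7.7 per group spread over three grades, averaging 2.6 per cell. For assumed rates of 5–10% against 1%, power was 24–84% for a four-category Chi-squared and 49–96% for a rank test.

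**The case against.** A reader might infer that the article prescribes Chi-squared for satisfaction. It does not. The classes are set out under data collection, and a 1–10 score is also numerical, so the t-test or Mann–Whitney route is open and the classes could be purely descriptive. The choice of test for each secondary outcome may also be left to an analysis plan that is not shown. This stands as far as it goes: the Chi-squared comparison is the natural reading, not a stated assignment. The point survives because it rests on two things the article does fix, the cut and the only test for categories, and not on an omission.

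A reader might also infer that the three-class test loses power whatever the difference. Check 3 refutes that. The minority pattern is plausible here, since the Discussion expects that the tube may cause discomfort or nasal injury, which could leave a few patients very dissatisfied while the rest notice nothing. This stands too. It limits the claim to a general shift and is the reason to keep the class table.

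Finally, nothing says that bleeding is compared by grade. Incidence would give a two-by-two table with no order to lose, so the bleeding remark is only conditional.

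**Conclusion.** The concern holds in limited form and is minor. Taken together, the stated rules lead to an unordered three-class comparison of a named secondary outcome for which a finer score is collected. For a general shift of 0.5 points, with assumed SD 1.5–2.0 and 140 per group, power is about 33–46%, against 50–76% with the raw score and a test already listed. The size rests on assumed distributions and does not carry over to a difference confined to a small dissatisfied group, where the ranking reverses. The type I error stays near 5%, and the hypoxemia result and the sample size are untouched.

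**What to change.** In Sample size estimation and statistical analysis, state that satisfaction of each rater is compared on the 1–10 score with the Mann–Whitney test already listed, and that poor, fair and good are reported as n (%) by group. Add that, if the 0–3 bleeding grade is compared, a rank or linear-trend test is used; if incidence is compared, say so.

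The cost is a sentence or two, with no new data or software. Trial status reports 20 participants recruited by 10 May 2018, so at that date the change could be made early in recruitment. The downside is less sensitivity to a difference confined to a small poor group. The class table keeps such a group visible but does not test it.
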